# 4.0 Justification of Methodology

The study trial shall involve 78 subjects as determined above. The trial shall last 84 days (12 weeks) which is greater than the mean treatment time for most trials reviewed and we feel enough time to determine whether a clinically significant effect will be produced. Longer duration would not likely show much more increased effect but rather might jeopardise the results through loss of participation and or incorporation of other treatments. The extended duration will ensure all active substances are metabolised and will allow for more accurate data collection on the effects of naturopathic medical treatments.

We employed a controlled design, rather than the conventional before/after design employed by many intervention studies as we wish to assess not only activity in the treatment group but also to determine if any change is significantly different from a control group not receiving the intervention. The absence of a control group would make it impossible to determine if variability in metabolism within individuals has overshadowed the potential impact of naturopathic medical treatments on anxiety symptoms. Examples of factors that could influence variability within individuals include changes in stimulant use, sleeping habits, compliance to treatment interventions, exercise levels and environmental stressors that may occur over the course of the study. Traditional drug intervention studies that are not controlled are inherently susceptible to bias and it is very difficult to determine if the results have been skewed.

**Setting:**

The Gateway Processing Plant is an ideal institution from which to adequately supervise and conduct the study. Study participants will be volunteers recruited from Canada Post employees through advertisements in corporate newsletters, information and talks led by the trial investigators. Participants will be fully informed of the treatment they may receive and must give informed consent before enrolment.

## 5.1 Time Line

The subjects will be directly involved in the study for twelve weeks. We intend on recruiting for the trial immediately upon approval of the trial by Health Canada. Recruitment should take three to six weeks and if possible be complete before the end of October. We will commence with treatment after recruitment of 80 eligible participants, which is projected to early November. The trial itself will be completed by the end of January 2006. Data analysis will ensue followed by publication in a peer reviewed article sometime in the Winter of 2006.

## 5.2 Ethics

We have passed this study through the internal review board at CCNM for ethics approval, please see the Research Ethics Board Attestation. Informed consent will be obtained from all enrolled subjects, please see Appendix D for Informed Consent forms. Management and assessment of health concerns will be under the direction of [name] MD.

## 5.3 Funding and industry involvement

Support for the study has been generously provided by Canada Post Corporation, Canadian Union of Postal Workers, and Swiss Herbals through the Research Department of the Canadian College of Naturopathic Medicine. Funding to the college is under the control of the chief financial officer at The Canadian College of Naturopathic Medicine, see appendix E. Beyond the confines of this trial, none of the investigators, nor the supervising physician involved have any ties or relationships with Swiss Herbals.

This trial was registered with the International Standard Randomized Clinical Trial Registry (trial registration number: ISRCTM78958974 available at <http://www.controlled-trials.com/isrctn/search.html?srch=ISRCTN78958974&sort=3&dir=desc&max=10>). Registration of this trial took place after the trial had been completed due to a number of complications with previous submissions and delays in the registration process. We additionally recognize a lack of knowledge on the part of the authors with regards to clinical trial registration – initially it was our understanding that because the trial was taking place within a workplace setting, registration was not necessary. After recognizing our error and misunderstanding, we proceeded with a registration attempt. We declare that this delay was **in no part** due to conflicts of interest, or an attempt to avoid open knowledge of the existence, conduct or results of the trial.

- 1. **Relevance**

Anxiety disorders are among the most prevalent psychiatric disorders in the Canada Post workers general population. Anxiety disorders are associated with considerable chronicity, morbidity, and disability. The economic costs of anxiety disorders include psychiatric, and nonpsychiatric emergency care; hospitalization; prescription drugs; reduced productivity; absenteeism from work; and suicide. We aim to evaluate the efficacy of typical Naturopathic treatment on anxiety. This will also lay the groundwork for an assessment of the cost effectiveness of Naturopathic Medicine in the treatment of anxiety in the work place.

.

# APPENDIX A BECK ANXIETY INVENTORY

Below is a list of common symptoms of anxiety. Please carefully read each item in the list. Indicate how much you have been bothered by that symptom during the past month, including today, by circling the number in the corresponding space in the column next to each symptom.

|  | Not At All | Mildly but it didn’t bother me much. | Moderately - it wasn’t pleasant at times | Severely – it bothered me a lot |
| --- | --- | --- | --- | --- |
| Numbness or tingling | 0 | 1 | 2 | 3 |
| Feeling hot | 0 | 1 | 2 | 3 |
| Wobbliness in legs | 0 | 1 | 2 | 3 |
| Unable to relax | 0 | 1 | 2 | 3 |
| Fear of worst happening | 0 | 1 | 2 | 3 |
| Dizzy or lightheaded | 0 | 1 | 2 | 3 |
| Heart pounding/racing | 0 | 1 | 2 | 3 |
| Unsteady | 0 | 1 | 2 | 3 |
| Terrified or afraid | 0 | 1 | 2 | 3 |
| Nervous | 0 | 1 | 2 | 3 |
| Feeling of choking | 0 | 1 | 2 | 3 |
| Hands trembling | 0 | 1 | 2 | 3 |
| Shaky / unsteady | 0 | 1 | 2 | 3 |
| Fear of losing control | 0 | 1 | 2 | 3 |
| Difficulty in breathing | 0 | 1 | 2 | 3 |
| Fear of dying | 0 | 1 | 2 | 3 |
| Scared | 0 | 1 | 2 | 3 |
| Indigestion | 0 | 1 | 2 | 3 |
| Faint / lightheaded | 0 | 1 | 2 | 3 |
| Face flushed | 0 | 1 | 2 | 3 |
| Hot/cold sweats | 0 | 1 | 2 | 3 |
| Column Sum |  |  |  |  |

## Scoring - *Sum each column. Then sum the column totals to achieve a grand score. Write that score here _______*

## Appendix B SF-36

Your Health and Well-Being

**This survey asks for your views about your health. This information will help keep track of how you feel and how well you are able to do your usual activities. *Thank you for completing this survey!***

**For each of the following questions, please mark an**  **in the one box that best describes your answer.**

1. In general, would you say your health is:

| Excellent | Very good | Good | Fair | Poor |
| --- | --- | --- | --- | --- |
|  |  |  |  |  |
| 1 | 2 | 3 | 4 | 5 |

**2. Compared to one year ago, how would you rate your health in general now**?

| Much better  now than one  year ago | Somewhat  better  now than one  year ago | About the  same as  one year ago | Somewhat  worse  now than one  year ago | Much worse  now than one  year ago |
| --- | --- | --- | --- | --- |
|  |  |  |  |  |
| 1 | 2 | 3 | 4 | 5 |

|  | Yes,  limited  a lot | Yes,  limited  a little | No, not  limited  at all |
| --- | --- | --- | --- |
|  |  |  |  |
| a Vigorous activities, such as running, lifting  heavy objects, participating in strenuous sports  1  2  3 | | | |
| b Moderate activities, such as moving a table, pushing  a vacuum cleaner, bowling, or playing golf  1  2  3 | | | |
| c Lifting or carrying groceries  1  2  3 | | | |
| d Climbing several flights of stairs  1  2  3 | | | |
| e Climbing one flight of stairs  1  2  3 | | | |
| f Bending, kneeling, or stooping  1  2  3 | | | |
| g Walking more than a kilometre  1  2  3 | | | |
| h Walking several hundred metres  1  2  3 | | | |
| i Walking one hundred metres  1  2  3 | | | |
| j Bathing or dressing yourself  1  2  3 | | | |

3. The following questions are about activities you might do during a typical day. Does your health now limit you in these activities? If so, how much?

4. During the past 4 weeks, how much of the time have you had any of the following problems with your work or other regular daily activities as a result of your physical health?

|  | All of  the time | Most of  the time | Some of  the time | A little of  the time | None of  the time |
| --- | --- | --- | --- | --- | --- |
|  |  |  |  |  |  |
| a Cut down on the amount of  time you spent on work or  other activities  1  2  3  4  5 | | | | | |
| b Accomplished less than you  would like  1  2  3  4  5 | | | | | |
| c Were limited in the kind of  work or other activities  1  2  3  4  5 | | | | | |
| d Had difficulty performing the  the work or other activities (for  example, it took extra effort)  1  2  3  4  5 | | | | | |

5. During the past 4 weeks, how much of the time have you had any of the following problems with your work or other regular daily activities as a result of any emotional problems (such as feeling depressed or anxious)?

|  | All of  the time | Most of  the time | Some of  the time | A little of  the time | None of  the time |
| --- | --- | --- | --- | --- | --- |
|  |  |  |  |  |  |
| a Cut down on the amount of  time you spent on work or  other activities  1  2  3  4  5 | | | | | |
| b Accomplished less than you  would like  1  2  3  4  5 | | | | | |
| c Did work or other activities  less carefully than usual  1  2  3  4  5 | | | | | |

6. During the past 4 weeks, to what extent has your physical health or emotional problems interfered with your normal social activities with family, friends, neighbors, or groups?

| Not at all | Slightly | Moderately | Quite a bit | Extremely |
| --- | --- | --- | --- | --- |
|  |  |  |  |  |
| 1 | 2 | 3 | 4 | 5 |

7. How much bodily pain have you had during the past 4 weeks?

| None | Very mild | Mild | Moderate | Severe | Very severe |
| --- | --- | --- | --- | --- | --- |
|  |  |  |  |  |  |
| 1 | 2 | 3 | 4 | 5 | 6 |

8. During the past 4 weeks, how much did pain interfere with your normal work (including both work outside the home and housework)?

| Not at all | A little bit | Moderately | Quite a bit | Extremely |
| --- | --- | --- | --- | --- |
|  |  |  |  |  |
| 1 | 2 | 3 | 4 | 5 |

9. These questions are about how you feel and how things have been with you during the past 4 weeks. For each question, please give the one answer that comes closest to the way you have been feeling. How much of the time during the past 4 weeks…

|  | All of  the time | Most of  the time | Some of  the time | A little of  the time | None of  the time |
| --- | --- | --- | --- | --- | --- |
|  |  |  |  |  |  |
| a Did you feel full of life?  1  2  3  4  5 | | | | | |
| b Have you been very nervous?  1  2  3  4  5 | | | | | |
| c Have you felt so down in the  dumps that nothing could  cheer you up?  1  2  3  4  5 | | | | | |
| d Have you felt calm and  peaceful?  1  2  3  4  5 | | | | | |
| e Did you have a lot of energy?  1  2  3  4  5 | | | | | |
| f Have you felt downhearted  and depressed?  1  2  3  4  5 | | | | | |
| g Did you feel worn out?  1  2  3  4  5 | | | | | |
| h Have you been happy?  1  2  3  4  5 | | | | | |
| i Did you feel tired?  1  2  3  4  5 | | | | | |

10. During the past 4 weeks, how much of the time has your physical health or emotional problems interfered with your social activities (like visiting with friends, relatives, etc.)?

| All of  the time | Most of  the time | Some of  the time | A little of  the time | None of  the time |
| --- | --- | --- | --- | --- |
|  |  |  |  |  |
| 1 | 2 | 3 | 4 | 5 |

11. How TRUE or FALSE is each of the following statements for you?

|  | Definitely  true | Mostly  true | Don’t  know | Mostly  false | Definitely  false |
| --- | --- | --- | --- | --- | --- |
|  |  |  |  |  |  |
| a I seem to get sick a little easier than other people  1  2  3  4  5 | | | | | |
| b I am as healthy as  anybody I know  1  2  3  4  5 | | | | | |
| c I expect my health to  get worse  1  2  3  4  5 | | | | | |
| d My health is excellent  1  2  3  4  5 | | | | | |

*Thank you for completing these questions!*

## Appendix c Fatigue questionnaire

Below you will find 20 statements regarding your health. With these statements we hope to get an impression of your health within the **past 2 weeks.**

If you find that the statement very **true**, put an **X** in the appropriate box, like this:

I feel relaxed yes, that is true ******** no, that is not true

If you find the statement **not true**, put an **X** in the appropriate box, like this:

I feel relaxed yes, that is true ******** no, that is not true

If you find the statement to be true sometime, and not true at others, place an X in the box in accordance to how you have felt

I feel relaxed yes, that is true ******** no, that is not true

1. I feel tired yes, that is true ******** no, that is not true

2. I feel very active yes, that is true ******** no, that is not true

3. Thinking requires effort yes, that is true ******** no, that is not true

4. Physically, I feel exhausted yes, that is true ******** no, that is not true

5. I feel like doing all kinds of nice things yes, that is true ******** no, that is not true

6. I feel fit yes, that is true ******** no, that is not true

7. I do quite a lot within a day yes, that is true ******** no, that is not true

8. When I am doing something

I can concentrate quite well yes, that is true ******** no, that is not true

9. I feel weak yes, that is true ******** no, that is not true

10.I don’t do much during the day yes, that is true ******** no, that is not true

11.I can concentrate well yes, that is true ******** no, that is not true

12. I feel rested yes, that is true ******** no, that is not true

13. I have trouble concentrating yes, that is true ******** no, that is not true

14. Physically I feel I am

in a bad condition yes, that is true ******** no, that is not true

15. I am full of plans yes, that is true ******** no, that is not true

16. I get tired quickly yes, that is true ******** no, that is not true

17. I have a low output yes, that is true ******** no, that is not true

18. I feel no desire to do anything yes, that is true ******** no, that is not true

19. My thoughts easily wander yes, that is true ******** no, that is not true

20. Physically I feel I am in good shape yes, that is true ******** no, that is not true

## Appendix F Patient questionaire and Recording sheets

#
[figure not shown]
THE CANADIAN COLLEGE OF NATUROPATHIC MEDICINE

**Treatment of anxiety amongst Canada Post workers: A randomized controlled trial**

# Principal investigator: [name]

# Study Co-ordinators: [name] and [name]

# Schedule of events (day)

| Activity | 0 | 1 | 28 | 56 | 84 |
| --- | --- | --- | --- | --- | --- |
| Inclusion/Exclusion Criteria | X |  |  |  |  |
| BAI | X |  | X | X | X |
| Urine Test to rule out Gross liver and Kidney Pathologies | X |  |  |  |  |
| Subject Consent Signed | X |  |  |  |  |
| Clinical Assessment | X | X | X | X | X |
| SF-36 and Fatigue Questionnaire |  | X | X | X | X |
| Dispense Study Supplements |  | X | X | X | X |
| Cognitive Behavioral Intervention (weekly) |  | X | X | X | X |
| Record Study Drug Use |  |  | X | X | X |
| Record Adverse Events |  |  | X | X | X |
| End Study Interview |  |  |  |  | X |
| Phone Contact Available | X | X | X | X | X |

#
[figure not shown]
THE CANADIAN COLLEGE OF NATUROPATHIC MEDICINE

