On subsequent visits, both the control and intervention group patients will receive treatments including cognitive behavioural stress reduction, behavioral psychotherapy, examination of sleep patterns and treatment for any insomnia. Both groups will be encouraged to engage in an active exercise routine. The active group will also receive daily good quality multi vitamin (Ultra Balance III by Douglas Labs) and *Withania somnifera* (300 mg standardized to 1.5% Withanolides, bid) (Ashwagandha by Douglas Labs). The control group will receive placebo identical in look and frequency of dosage to the treatment group. On subsequent visits, the active group will receive lifestyle and diet counseling, and will continue with behavioral psychotherapy. Active group patients will also receive acupressure massage for at least 15 minutes once per week.

Both the active and control arm will attend weekly 30 minute treatments, for a total of 12 treatments over 12 weeks. Both groups will complete the Beck Anxiety Inventory, S-90-R, SF-36, Fatigue Questionnaire, and the Perceived Benefit of Treatment questionnaires at 4, 8, and 12 weeks. At these times, the sitting and orthostatic blood pressures will also be recorded. Both groups will also hand in the Pain Diet, Absenteeism, Pain Medication and Therapies Diary every week.

Study period is 12 weeks. Clinical evaluations will be performed at:

- Baseline (Visit 1 - Day 1)
- Interim for the treatment groups: (Visit 2 - Day 7, Visit 3- Day 14, Visit 4 – Day 21, Visit 4 – Day 28, Visit 5 – Day 35, Visit 6 – Day 42, Visit 7 – Day 49, Visit 8 – Day 56, Visit 9 – Day 63, Visit 10 – Day 70, Visit 11 – Day 77)
- Interim for the control groups: (Visit 2 - Day 7, Visit 3- Day 14, Visit 4 – Day 21, Visit 4 – Day 28, Visit 5 – Day 35, Visit 6 – Day 42, Visit 7 – Day 49, Visit 8 – Day 56, Visit 9 – Day 63, Visit 10 – Day 70, Visit 11 – Day 77)
- End of Treatment (Visit 12 - Day 84), Questionnaires and Medication diaries filled in for the last time

Follow-up data will be collected at 2, 6, and 12 months post treatment via a mailed questionnaire package containing the Beck Anxiety Inventory, S-90-R, SF-36, Fatigue Questionnaire, and the Perceived Benefit of Treatment questionnaires, as well as the Diet, Absenteeism, Medication and Therapies Diary. Non-responders will receive reminders by post. If this is unsuccessful, the patients will be telephoned.

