## 3.3 Timeline

1. Labelled as day 0, all potential candidates will be screened for inclusion/exclusion criteria by being asked to read and sign the informed consent, fill in questionnaires including the BAI, be clinically assessed, have their blood pressure taken, and have urine tests to assess for proper liver and kidney function.

1. On day 1, participants that have fulfilled all eligibility criteria and completed the consent form will be randomised into either treatment or control groups using a random number generator by the research assistant who will label the containers of placebo, *Withania somnifera* and multivitamin respectively.
2. Both treatment and placebo groups shall receive the visually identical capsules by the study co-ordinator with instructions on the dosage schedule.
3. Both groups shall take their medications twice daily, one capsule in the morning and one in the evening prior to meals.
4. The treatment shall last 90 days.
5. On day 1, subjects will be clinically assessed, have their blood pressure taken, be interviewed, and complete the SCL-90R, SF-36 and fatique questionnaires. Medication usage will be monitored and compliance to the interventions will be assessed.
6. On day 7, subjects will receive cognitive–behavioral therapy, dietary advice and stress reduction techniques. They will continue these treatment sessions 1 time per week until the completion of the study. (Day 14, 21, 28, 35, 42, 49, 56, 63, 70, 77 and 84)
7. On day 8, subjects in the active group will receive acupressure massage in the treatment of anxiety. They will continue these treatment sessions 1 time per week until the completion of the study. . (Day 15, 22, 30, 38, 45, 52, 60, 68, 75, 82 and 90)
8. On day 28, subjects will be clinically assessed, have their blood pressure taken, be interviewed, and complete the SCL-90R, SF-36 and fatigue questionnaires
9. On day 56, subjects will be clinically assessed, have their blood pressure taken, be interviewed, and complete the SCL-90R, SF-36 and fatigue questionnaires
10. On day 84, subjects will be clinically assessed, have their blood pressure taken, be interviewed, and complete the SCL-90R, SF-36 and fatigue questionnaires

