Adherence to the schedule and adverse effects will be assessed at patient interviews at each stage of the study. In addition, subjects will have access by phone or visit to the supervising physician if they feel their health is being compromised in any way during the study. As a way of measuring and promoting compliance, subjects will be given study calendars and asked to return their unfinished pills.

.

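### Adverse-event recording is scheduled only on Days 28, 56 and 84, so 9 of the 12 weekly sessions have no scheduled record, and no other section sets a different frequency

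*Protocol*

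**What the plan says.** The schedule of events in Appendix F has columns for five days, "Activity | 0 | 1 | 28 | 56 | 84", and its safety row, "Record Adverse Events", is marked on the last three of them only: "Record Adverse Events | | | X | X | X". Another row of the same table is labelled "Cognitive Behavioral Intervention (weekly"); the adverse-event row carries no such label. Supplements are dispensed on Days 1, 28, 56 and 84.

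The Methodology section states: "Both the active and control arm will attend weekly 30 minute treatments, for a total of 12 treatments over 12 weeks". Section 3.3 lists those sessions by day, from Day 7 to Day 84. It specifies an interview on Days 1, 28, 56 and 84 and then says: "Adherence to the schedule and adverse effects will be assessed at patient interviews at each stage of the study". It does not define a stage. The Safety part of the introduction promises periodic monitoring and documentation of adverse events, without an interval.

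On duration, section 3.3 says "The treatment shall last 90 days", while section 4.0 gives the trial 84 days and the Methodology section gives 12 weeks. On acupressure, section 3.3 says "On day 8, subjects in the active group will receive acupressure massage in the treatment of anxiety" and lists further sessions up to Day 90. The Methodology section mentions weekly acupressure of at least 15 minutes for the active arm but does not say whether it is a separate visit.

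**The concern.** The abstract (section 2.0) and section 3.0 both name safety as something the trial will evaluate, and the Safety section stresses the public importance of detecting harm. How often adverse events are actively sought is a matter for the protocol. Here the only explicit frequency is four-weekly, although a practitioner sees each participant every week.

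Three things are at stake. First, a mild or short-lived event early in an interval must be remembered for up to four weeks or volunteered in the meantime. Second, volunteered reports depend on opportunity, and the active arm may have more contacts than the control arm. Third, if supplements continue after Day 84, events in that period have no scheduled record. The follow-up mailings at 2, 6 and 12 months do not list an adverse-event form either.

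**Working it through.** **Weekly sessions.** Section 3.3 gives Days 7, 14, 21, 28, 35, 42, 49, 56, 63, 70, 77 and 84. That is 12, which reproduces the 12 treatments stated in the Methodology section.

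**Sessions with a scheduled adverse-event record.** The schedule of events gives Days 28, 56 and 84, which is 3.

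**Sessions without one.** 12 − 3 = 9 (Days 7, 14, 21, 35, 42, 49, 63, 70 and 77), and 9/12 = 75%. Counting the Day 1 baseline visit as well gives 13 − 3 = 10 of 13.

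**Recall interval.** Successive scheduled records are 56 − 28 = 28 days and 84 − 56 = 28 days apart. Recording at the existing sessions would make the interval 7 days.

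**Do other sections set a different frequency?**
- Table layout: the other weekly visits have no column, so a blank cannot be read for them directly. But the table does have a way to mark a weekly activity, and it uses it for the cognitive-behavioural row only.
- Section 3.3: adverse effects are tied to interviews, and the interviews named are on Days 1, 28, 56 and 84. Day 1 is when supplements are first dispensed, so the on-treatment interviews fall on the same three days as the table.
- Safety section: no interval is given.
- Methodology section: the weekly visits are called clinical evaluations, but no adverse-event question is assigned to them.
- Concomitant-medication form: changes are asked about on Days 1, 28, 56 and 84, plus an unspecified other day. This fits the four-weekly pattern.

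**Contacts by arm.** Section 3.3 lists acupressure on Days 8, 15, 22, 30, 38, 45, 52, 60, 68, 75, 82 and 90, which is 12 days, none of them a weekly session day.
- If these are separate visits, the active arm has 12 + 12 = 24 contacts after baseline against 12 in the control arm, and 24 − 3 = 21 of the 24 have no scheduled record.
- If acupressure is given within the weekly visit, as the Methodology section can be read, contacts are 12 in each arm.

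**End of treatment.** If the 90-day statement holds, 90 − 84 = 6 days fall after the last scheduled record. If the 84-day statement holds, no such period is planned, but the Day 84 mark in the dispensing row then needs explaining.

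**The case against.** The strongest reply is that a four-weekly query is a legitimate design, since it can ask about the whole interval since the last one. That stands: the schedule is not wrong simply because it is four-weekly.

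A reader might go further and infer that the nine other sessions produce no safety information. The documents do not support that. The Safety section says adverse events will be documented and does not limit this to three days. Section 3.3 gives phone or visit access to the supervising physician. The recording sheets allow an extra assessment day, and there are withdrawal and adverse-event forms. A diary handed in every week covers medication and absence, though it is not an adverse-event form. What these routes lack is a scheduled question put to every participant.

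Nor does the rule on discontinuing when health is compromised depend on this table row. It acts when the participant or the qualified investigator judges it necessary, and participants are seen weekly.

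The objection on contacts also stands in part: 24 against 12 rests on section 3.3 alone. The scheduled query is identical in both arms, so any imbalance concerns only reports volunteered off schedule and then recorded.

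**Conclusion.** The point holds as a gap in scheduling and wording. Nine of 12 weekly sessions have no scheduled adverse-event record, the recall interval is 28 days where 7 is available at visits already planned, and the general statements in the Safety section and section 3.3 do not set another frequency. The count needs no assumption beyond taking the table and the named interview days at face value.

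Two parts are conditional. Unequal opportunity to volunteer applies only if acupressure is a separate visit. The uncovered period applies only if treatment continues after Day 84, and lasts 6 days under the 90-day statement.

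Two stronger conclusions are tempting and should not be drawn. One is that the trial's safety conclusion is unreliable: the scheduled query is the same in both arms and other reporting routes exist. The other is a figure for the share of events missed: the documents give no recall rate, and weekly questioning would not achieve perfect detection either. The change is worth making because it is specific and cheap.

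**What to change.** - In the schedule of events, mark the adverse-event row as weekly, Days 7 to 84, in both arms, with the same fixed question.
- Reword the Safety section and the adherence and adverse-effects paragraph of section 3.3 to state that frequency.
- Reconcile the 84-day and 90-day statements and the Day 84 dispensing mark. Then make sure that the last adverse-event record, in both arms, does not come before the end of supplement use.
- State whether acupressure is given within the weekly visit or separately, so that sections agree on the number of contacts per arm.

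**Cost.** One form line at each existing visit: 9 more entries per participant, or at most 9 × 80 = 720 if all 80 planned participants attend every session. The count of minor events will be somewhat higher. No extra visit is needed for the weekly recording. If supplement use is found to run past Day 84, one further contact per participant would be needed, because the Day 90 session in section 3.3 is for the active arm only.
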